## 3. Evaluation of the Feasibility and Impact of SUPRANET

The purpose of the evaluation is to investigate the activities of SUPRANET by examining its feasibility and impact on suicidal ideation and behaviour.

This study aims to answer:(1)Does the implementation strategy of SUPRANET lead to the expected EAAD outcomes [6,7,8,9] in terms of:
(a)Reduced suicidal ideation and behaviour and psychological distress?(b)Reduced stigma and taboo and improved attitude towards seeking help?(c)Increased help seeking behaviour to the helpline of 113 Suicide Prevention? (2)Is SUPRANET implemented as intended, in terms of:
(a)What is the reach on each SUPRANET program component (the actors, situations, sites, and contexts involved in the SUPRANET implementation process)?(b)What are the barriers and facilitators when implementing the SUPRANET approach?(c)What is the impact of the interventions on professional performance?

The evaluation of the feasibility and impact on the Dutch SUPRANET communities will be carried out by the research department of 113 Suicide Prevention, NIVEL (Netherlands Institute for Health Services Research), and local Public Health Services in the participating communities.

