### 3.2. Evaluation of the Impact of SUPRANET

#### 3.2.1. Suicidal Ideation and Behaviour and Psychological Distress of the General Public

Suicidal ideation and behaviour of the general public will be measured in two ways: First, while challenging, because of the low base rate of completed suicide (11 per 100,000 in The Netherlands), suicide rates will be analysed using data from Statistics Netherlands. Trends in suicide rates during 2017–2019 in the seven SUPRANET communities will be compared to the national suicide trends. In 2015, the number of suicides in the SUPRANET communities was 166, on a population of 1,407,331 (11.8 per 100,000). Differences in suicide rates at baseline and after each implementation year will be calculated using incidence rate ratios. The hypothesis is that the multilevel intervention approach of SUPRANET will lead to a reduction in the suicide rate in the general population, as was found in other EAAD studies [6,7,8,9].

Secondly, the scores on the Suicidal Ideation Attribution Scale [15] in an online survey will be analysed. Four measurements will be carried out using on-line questionnaires among the general population. In each measurement, the national sample will be 1000 and the SUPRANET community sample will be 700 (in each SUPRANET community *n* = 100). The sample will be stratified by gender, age, education, region, and social class. The first measurement, the baseline, took place in January 2017. The second will take place just after the first wave of the public awareness campaign, the third in January 2018, and the fourth in January 2019. A fresh sample is taken for each of the four measurements to prevent learning effects and keep the comparison pure over time. Given an alpha of 0.05 and a power of 0.8, the sample will allow us to detect a small effect size of 0.08. The Suicidal Ideation Attribution Scale (SIDAS) consists of five items that are scored from 0 to 10 and assesses the frequency and controllability of suicidal thoughts, as well as the closeness to a suicide attempt, distress and interference with daily activities. We will investigate, using General Linear Model (GLM) repeated measures, if the changes measured in the SUPRANET communities are more improved than the changes measured nationally.

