#### 3.3.4. Impact of the Intervention on Professional Performance: Identification of Depression and Suicide (Attempt) within Primary Care

Using the NIVEL primary care database (NIVEL-PCD) we can extract incidence and prevalence rates of depression and suicide (attempt) for individual general practice. NIVEL-PCD is one of the largest primary care databases in Europe, covering more than 500 GPs with a total practice population of 1.6 million individuals. NIVEL-PCD collects routine electronic health record data, including health problems, consultations, prescriptions, and referrals. Health problems are ICPC coded (international classification of primary care) [25]. The database is representative of the Dutch population. If practices are participating in the intervention, but not yet connected to the NIVEL-PCD, we will include the practices in the NIVEL PCD for the time of the study. Within participating GP practices in all seven regions we will collect all registrations of P76 (depression), P03 (depressed feeling) and P77 (suicide (attempt) and compare the rates 12 months before the start of the project (January–December 2016) to those 12 months after the end of the two year program (January–December 2019). An increase in incidence is hypothesized, due to an increase in recognition of depression and suicidal behaviour within primary care after the suicide prevention training offered to GPs and mental health nurses in the SUPRANET communities. Within the GPs, for the year 2015, an incidence of 11.4 per 1000 patients with P76 (depression) was found, and an incidence of 9.6 for P03 (depressed feeling) For a standard practice with about 2500 patients, we expect around 30 new cases of P76 per year and 25 new cases of P03 per practice. Within one region with five GPs, we expect 275 new registrations of depression and depressive thoughts. Within the seven regions we expect around 1900 new cases of depression. Within the NIVEL registration, we will use a matched control group of around 30–40 practices. Given an alpha of 0.05 and a power of 0.8, this will allow us to detect a small effect size of 0.10.

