Analysis will be carried out using multilevel regression techniques, with the incidence of depression and suicidal thoughts as the dependent variable and the condition (intervention or control) as the independent variable. Covariates will be the characteristics of the practices (urban/rural, distribution of age, solo practice, or group practice) and the incidence of depression and suicidal thoughts before the intervention. The different levels are the region, the general practice and the patient.

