## 4. Discussion

113 Suicide Prevention has the ambition to implement SUPRANET nationwide. The results of this study will help other regions to more effectively tailor the program to their context, important for the national implementation of the EAAD in The Netherlands. The results will be of high relevance for countries in and outside of Europe.

As suicides have been rising since 2007 in The Netherlands, 113 Suicide Prevention believes it is time to really tackle the problem, and directly target suicidal behaviour. While the focus of the public awareness campaign of the EAAD lies on depression, with the secondary aim to reduce suicidal behaviour, in SUPRANET we decided to directly focus on suicide. We believe the specific focus fits well in the Dutch culture, since the Dutch expect others to be open and direct. Furthermore, general practitioners and gatekeepers in The Netherlands are confronted with suicidal behaviour more often than before. Therefore, they understand the need for an intervention with a specific focus on suicide prevention. Regarding the public awareness campaign, we know from the literature that properly communicating about suicide can actually result in less suicidal behaviour (Papageno effect). 113 Suicide Prevention appoints to the subject suicide direct and encourages people to talk about it. Still, as it is a novum to offer a public campaign on suicide prevention in The Netherlands, a safety procedure is built in. As soon as any rise in adverse events are reported, either via the national railways or via other monitors, such as social media, the campaign will immediately be aborted.

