**Figure 2 ijerph-14-00349-f002:**
[figure not shown]
The four level approach of SUPRANET Community, based on the European Alliance against Depression (EAAD).

**Table 1 ijerph-14-00349-t001:** Outcomes and measurements per target group.

Evaluation	Target Group	Compared to Baseline and to National Level, Does Being a SUPRANET Community Have an Impact on:	Measurement	Source
Part 1	General Public	Severity of suicidal ideation and behaviour	Suicide trends	Statistics Netherlands
			Suicidal Ideation Attributes Scale [15]	Online Survey 113
		Psychological distress	Kessler Psychological Distress Scale (K10) [16]	Dutch Health Monitor Public Health Services
		Public attitudes, stigma and taboo	Depression Stigma Scale [17]	Online Survey 113
			Attitude towards seeking professional psychological help short form [18]	Online Survey 113
			Questions on suicide experiences and perceived taboo	Online Survey 113
		Help-seeking behaviour	Change in monthly crisis calls to 113 during intervention compared with previous year	113
Part 2	Community facilitators	Identification of people with suicidal thoughts and linking to professional care	Number of people screened and linked to professional care in previous month	113
		Attitude and confidence	Questions on attitude toward suicide and confidence in assessing and managing suicidal patients	113
	General Practitioners	Identification of patients with depressive symptoms and suicide(attempt) in primary care	Change in recognition of depression and suicidal behaviour within primary care	NIVEL/Primary Care Database Sentinel Practices
		Compliance to professional standards and guidelines regarding the exploration of suicidal behaviour with patients presenting with depressive symptoms	Questions on the exploration of suicidal behaviour and what actions/interventions were proposed/agreed upon. The questions are added in Appendix A.	NIVEL/Primary Care Database Sentinel Practices

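### One hypothesised increase covers depression codes and the suicide/attempt code P77 alike, so a rise in P77 cannot be read as better recognition; the model's outcome, suicidal thoughts, is not among the codes collected

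*Protocol article*

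**What the plan says.** All places are in the protocol article.

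- **Data collected (Section 3.3.4).** In participating practices "we will collect all registrations of P76 (depression), P03 (depressed feeling) and P77 (suicide (attempt) and compare the rates" between January–December 2016 and January–December 2019. Around 30–40 matched practices serve as controls.
- **Hypothesis (Section 3.3.4).** "An increase in incidence is hypothesized, due to an increase in recognition of depression and suicidal behaviour within primary care". The reason given is the training offered to GPs and mental health nurses. No code is exempted.
- **What P77 covers (Section 3.3.4, guideline-adherence paragraph).** The sentinel practices have used this code for patients after both fatal and non-fatal attempts.
- **Programme aims.** Research question 1(a) in Section 3 asks about "Reduced suicidal ideation and behaviour and psychological distress". Section 3.2.1 hypothesises that "SUPRANET will lead to a reduction in the suicide rate in the general population".
- **Model (Section 3.3.4).** A multilevel regression is planned "with the incidence of depression and suicidal thoughts as the dependent variable". The covariates include "the incidence of depression and suicidal thoughts before the intervention".
- **Table 1, GP row.** The outcome is named as "Identification of patients with depressive symptoms and suicide(attempt) in primary care".

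**The concern.** There are two linked problems.

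**Direction.** For P76 and P03, more recording after training is a natural sign of better case-finding. P77 is different, because it is a count of the events the programme exists to prevent. Better recording pushes it up and successful prevention pushes it down, while a real increase in attempts would also push it up. With a single expected direction over all three codes, a rise in P77 could be taken as evidence of better professional performance when it reflects more attempts. A fall caused by prevention could be taken as a lack of improvement.

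**Outcome definition.** The model paragraph analyses something other than what the data paragraph collects. As written, an analyst cannot tell whether the suicidal component of the outcome is P77, something taken from the questionnaire, or a composite with the depression codes. The baseline covariate has the same gap.

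The article says the results are meant to guide national implementation, so both points are better settled before the 2019 data are read.

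**Working it through.** **1. Which codes the hypothesis covers.** Three codes are collected. The hypothesis speaks of depression and of suicidal behaviour. P76 and P03 are the depression side, and P77 is the only code for suicidal behaviour. The expected increase therefore includes P77.

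**2. Which codes the sizing covers.** The inputs are in Section 3.3.4: incidences of 11.4 (P76) and 9.6 (P03) per 1000, 2500 patients per practice, five practices per region and seven regions.

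- P76: 0.0114 × 2500 = 28.5, stated as around 30.
- P03: 0.0096 × 2500 = 24.0, stated as 25.
- Per region: (30 + 25) × 5 = 275, as stated.
- Seven regions: 275 × 7 = 1925, stated as around 1900. Without rounding: (28.5 + 24.0) × 35 = 1837.5.

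The plan's figures reproduce from P76 and P03 alone. No incidence or expected count is given for P77 or for suicidal thoughts.

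**3. Whether P77 can separate recording from occurrence.** Write recorded P77 = true events × fraction recorded. Then

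fraction recorded after = (ratio of recorded P77 × fraction recorded before) ÷ ratio of true events.

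Take a 10% rise in recorded P77 (ratio 1.10). For the true change use −24%, 0 and +24%; 24% is the decline in suicidal acts that the Introduction reports for the Nuremberg programme. The fraction recorded before is not in the documents, so 40%, 50% and 60% are assumed.

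| Recorded before (assumed) | True events −24% | No true change | True events +24% |
|---|---|---|---|
| 40% | 57.9% | 44.0% | 35.5% |
| 50% | 72.4% | 55.0% | 44.4% |
| 60% | 86.8% | 66.0% | 53.2% |

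Example: 1.10 × 0.50 ÷ 0.76 = 0.724. The entries are the fractions recorded afterwards that produce the same 10% rise. Each is a possible value, so the P77 rate alone cannot tell the three situations apart.

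The matched controls do not resolve this. They remove trends common to both groups, but the programme is meant to change both recording and occurrence in the intervention regions.

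**4. Whether suicidal thoughts can be built from the collected data.** Setting the places side by side:

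| Place | Suicidal component named |
|---|---|
| Section 3.3.4 heading and code list | suicide (attempt), P77 |
| Table 1, GP identification row | suicide (attempt) |
| Section 3.3.4, dependent variable | suicidal thoughts |
| Section 3.3.4, baseline covariate | suicidal thoughts |

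The only GP data on suicidal thoughts come from the questionnaire in Appendix A. It is triggered by P76 contacts and asks whether thoughts were explored and, if so, what the patient answered. Its denominator is patients registered with depression, and the answer exists only for those who were asked. It yields a proportion explored, which suits the guideline-adherence question, and not an incidence in the practice population.

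**The case against.** The strongest reply is that P77 here belongs to research question 2(c), impact on professional performance. Table 1 lists it in Part 2 as a change in recognition. Question 1(a) is measured elsewhere, by suicide statistics, the SIDAS and the K10. Expecting trained GPs to record more while fewer people in the population die by suicide is a coherent pair of hypotheses. This stands as a statement of intent, and for that reason the two sections are not in flat contradiction. It does not repair the measure, because a recorded P77 rate still carries occurrence within it.

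Three stronger readings might be inferred, and the documents do not support them:

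- **That the plan has a rule scoring a P77 rise as success and a fall as failure.** Section 3.3.4 states a hypothesis and a mechanism, and no such rule.
- **That the Discussion's safety procedure ("As soon as any rise in adverse events are reported") conflicts with the hypothesis.** That sentence concerns aborting the public awareness campaign on signals from the railways or other monitors such as social media. It does not mention GP records, and the P77 follow-up year comes after the two-year programme.
- **That P77 is too rare to inform any claim.** The article gives no P77 incidence and makes no power claim for it, so this would rest entirely on an assumed rate.

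It can also be said that P76 and P03 mix recording with occurrence, since question 1(a) also seeks less psychological distress. That is true and calls for caution in interpretation. The difference is that P77 counts the targeted behaviour itself, including deaths that Section 3.2.1 expects to fall.

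Finally, suicidal thoughts may be loose shorthand for P77; the section uses terms loosely elsewhere. That is plausible, and it would make the correction easier. The phrase still appears twice in the model specification and disagrees with both the code list and Table 1. A fuller plan may define the outcome, but the published text states it inconsistently with its own data.

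**Conclusion.** The point holds in a limited form. One of the three codes, P77, is given an expected direction that cannot be read as better recognition without outside information. Two elements of the model, the dependent variable and the baseline covariate, name a quantity that the collected codes do not contain.

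Both conclusions rest on the text. The assumed recording fractions only illustrate the ambiguity; across 40% to 60%, the same 10% rise fits a real fall, no change or a real rise. The plan's case counts are unaffected, because they use P76 and P03 only. The finding does not show that the aims contradict each other, that the sponsor would report harm as success, or that the P77 analysis is underpowered.

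**What to change.** All changes are to the wording of Section 3.3.4.

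1. Limit the hypothesis that an increase reflects better recognition to P76 and P03.
2. Analyse P77 as a separate outcome with no presumed favourable direction, and interpret it alongside the suicide-rate data of Section 3.2.1.
3. In the multilevel model, replace the reference to depression and suicidal thoughts, in both the dependent variable and the baseline covariate, with P76/P03 and, in a separate model, P77. Leave suicidal thoughts to the Appendix A questionnaire and the guideline-adherence question.

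The cost is one additional model and giving up any claim of improved recognition based on P77. No new data are needed, and the stated case counts do not change.

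### The primary-care power statement (effect size 0.10, 80% power) has no defined metric and no stated allowance for practice and region clustering, so it is not supported for the planned multilevel analysis

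*Protocol article*

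**What the plan says.** Section 3.3.4 starts from the 2015 incidence of P76 (11.4 per 1000) and P03 (9.6 per 1000). For a practice of about 2500 patients it states "we expect around 30 new cases of P76 per year and 25 new cases of P03 per practice". It scales this to 275 registrations in a region with five practices, and then: "Within the seven regions we expect around 1900 new cases of depression". A matched control group of around 30–40 practices is added, and the conclusion is "Given an alpha of 0.05 and a power of 0.8, this will allow us to detect a small effect size of 0.10".

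Section 2.2.4 makes five practices per region a minimum, so 35 intervention practices is the smallest intended number. The analysis in section 3.3.4 is a multilevel regression of incidence on condition, adjusted for practice characteristics and pre-intervention incidence: "The different levels are the region, the general practice and the patient". The hypothesis is directional ("An increase in incidence is hypothesized"). The article gives no formula, effect metric, sidedness, intraclass correlation (ICC), between-practice variance or design effect.

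**The concern.** The power sentence and the analysis describe different information. The sentence rests on counts of new cases. The analysis compares practices, nested in regions, on their incidence. New cases are the numerator of that incidence, and practices differ in how readily they code depression. Whatever variation remains after baseline adjustment adds to the standard error and does not shrink as more cases accrue per practice.

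The figure also cannot be interpreted as printed. An effect size of 0.10 could be a 10% rise in incidence, a standardised difference between cases, or a standardised difference on the proportion of registered patients with a new code. These are very different targets.

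At stake is the reading of a null or imprecise result on recognition in primary care. A reader who takes 80% power at face value could conclude that a modest increase had been ruled out when the design could not show one.

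**Working it through.** **Inputs from the article.** Two-sided alpha 0.05 (sidedness assumed) and power 0.80, so z = 1.960 + 0.842 = 2.802. Intervention practices 7 × 5 = 35; control practices 30–40. Cases per practice 30 + 25 = 55, so 35 × 55 = 1925 intervention cases (stated as about 1900) and 30 × 55 = 1650 to 40 × 55 = 2200 control cases.

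**Step 1: reproduce 0.10 with independent cases.** The SE of the log rate ratio is √(1/e1 + 1/e0), and the detectable ratio is exp(2.802 × SE).
- 30 controls: SE = √(1/1925 + 1/1650) = 0.0336; detectable ratio 1.099; power at 1.10 is 81%.
- 35 controls: SE = 0.0322; ratio 1.095; power 84%.
- 40 controls: SE = √(1/1925 + 1/2200) = 0.0312; ratio 1.091; power 86%.

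With unrounded rates (11.4 × 2.5 + 9.6 × 2.5 = 52.5 per practice) and 30 controls, the ratio is 1.101 and power 79%. A standardised difference between independent cases gives 0.094–0.087, near 0.10 but a looser match. The stated figure is therefore matched most closely by a rate ratio of about 1.10 with no clustering.

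**Step 2: how much clustering this leaves room for.** With residual between-practice CV *c* after baseline adjustment, SE² = 1/e1 + 1/e0 + c²(1/35 + 1/n0), where n0 is the number of control practices. For 80% power at 1.10, SE² may be at most (ln 1.10 / 2.802)² = 0.001157.
- n0 = 30: c² = (0.001157 − 0.001126)/0.0619, so c ≈ 0.02.
- n0 = 40: c² = (0.001157 − 0.000974)/0.0536, so c ≈ 0.06.

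**Step 3: range of assumed CV.** The article gives none, so these values are assumptions. Each range runs over 30 to 40 controls.

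| Residual CV (assumed) | Power at ratio 1.10 | Detectable ratio, 80% power |
|---|---|---|
| 0 | 81–86% | 1.10–1.09 |
| 0.05 | 76–82% | about 1.10 |
| 0.10 | 63–69% | about 1.12 |
| 0.20 | 36–40% | 1.18–1.17 |
| 0.30 | 21–24% | 1.26–1.24 |

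Region-level variance, with seven intervention regions, is not included and would lower power further.

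**Step 4: P76 alone.** The 1900 combines both codes. P76 alone gives 11.4 × 2.5 × 35 ≈ 1000 cases (35 × 30 = 1050 with the article's rounding). With no clustering the detectable ratio is about 1.13–1.14, and power at 1.10 is about 53–62%.

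**Step 5: the other reading.** As a standardised difference on the 2.1% of registered patients with a new code, 0.10 × √(0.021 × 0.979) = 0.0143. That takes 2.1% to about 3.5%, a rise of 0.0143/0.021 = 68%.

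**The case against.** **The authors' formula is not shown.** This stands. That cases were counted as independent is inferred from the arithmetic. On the standardised-difference scale between cases, an ICC of about 0.002–0.006 would also yield 0.10, so a very small clustering allowance cannot be excluded.

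**The analysis handles clustering, and baseline adjustment recovers precision.** This also stands. The model has the right levels and adjusts for earlier incidence. On the case-level standardised scale, with an assumed baseline correlation of 0.7–0.8, power at 0.10 is 75–84% at ICC 0.01, 67–78% at 0.02 and 49–63% at 0.05. So 80% can be met at very low clustering, or in some cases at ICC 0.01 with strong adjustment. Recruiting more than five practices per region would help too. But a suitable model does not make a power figure right if that figure left out the model's variance components.

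**A condensed article may leave the ICC to a fuller document.** That is fair as to detail. Here, however, the article prints a specific power conclusion, with an undefined metric, beside the clustered analysis it is meant to support.

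**Stronger readings that a reader might infer.** One is that 80% power is definitely not delivered. The documents do not support that: it depends on a CV they do not give, and if 0.10 meant the 68% rise in step 5, power would be near 100% even at CV 0.30, before region variance. That reading is less likely, because the text builds on case counts and calls the effect small. Another is that this undermines the study's main result. Section 3.1 puts the primary outcomes on suicidal ideation and behaviour and attitudes toward them, and places professional performance in the feasibility study. A third is that the 1900 is an error of substance. The preceding sentence makes clear that the count joins depression and depressive thoughts, so this is a loose label.

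**Conclusion.** The claim of 80% power to "detect a small effect size of 0.10" is not supported for the analysis the article plans. The metric is undefined, and the figure is matched most closely by independent case counts, with no stated allowance for practice or region clustering.

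On the rate-ratio reading there is almost no slack, and power falls below 70% once the residual CV reaches 0.10. The conclusion rests on three assumptions: that 0.10 means a 10% increase in incidence, that the test is two-sided, and that residual between-practice variation lies in the tabulated range. The P76-only shortfall needs only the first two, since it appears without any clustering. This is a correction to a secondary power statement; it does not show that the comparison is uninformative.

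**What to change.** In section 3.3.4:

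1. Define the effect as an incidence rate ratio and state the sidedness of the test.
2. Replace the 0.10 with the detectable ratio for at least 35 versus 30–40 practices under the planned multilevel, baseline-adjusted model. State the range assumed for residual between-practice variation (or the ICC with the baseline correlation) and how region variance is treated. Past practice-level rates in the NIVEL database could inform that range.
3. Give the figure separately for P76 and for P76 plus P03.
4. Label the 1900 as P76 plus P03 registrations, of which about 1000 are P76.

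The cost is wording, a short recalculation and a less favourable figure. Drawing more control practices from the database is optional and not part of this correction: at CV 0.20, 140 controls would bring the detectable ratio only from about 1.18 (with 35 controls) to about 1.14.
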